## Abstract

**Background:**

The traditional spoon-feeding approach to introduction of solid foods during the complementary feeding period is supported by consensus in the scientific literature. However, a method called Baby-Led Introduction to SolidS (BLISS) has been proposed as an alternative, allowing infants to self-feed with no adult interference. To date, there have been no trials in the Brazilian population to evaluate the effectiveness of BLISS in comparison to the traditional approach.

**Methods/design:**

To evaluate and compare three different complementary feeding methods. Data on 144 mother-child pairs will be randomized into intervention groups by methods: (A) strict Parent-Led Weaning; (B) strict Baby-Led Introduction to SolidS; and (C) a mixed method. Prospective participants from Porto Alegre, Brazil, and nearby cities will be recruited through the Internet. The interventions will be performed by nutritionists and speech therapists, at 5.5 months of age of the child, at a private nutrition office equipped with a test kitchen where meals will be prepared according to the randomized method. The pairs will be followed up at 7, 9, and 12 months of age. Data will be collected through questionnaires designed especially for this study, which will include a 24h child food recall, questionnaires on the child’s and parents’ eating behavior, oral habits, eating difficulties, and choking prevalence. At 12 months of age, children will undergo blood collection to measure hemoglobin, ferritin, and C-reactive protein, saliva collection for analysis of genetic polymorphisms, and oral examination. Anthropometric parameters (child and maternal) will be measured at the baseline intervention, at a 9 month home visit, and at the end-of-study visit at the hospital. The primary outcome will be child growth and nutritional status *z*-scores at 12 months; secondary outcomes will include iron status, feeding behavior, acceptability of the methods, dietary variety, choking, eating behaviors, food preferences, acceptance of bitter and sweet flavors, suction, oral habits, oral hygiene behavior, dental caries, gingival health status, and functional constipation.

**Discussion:**

The trial intends to ascertain whether there are potential advantages to the BLISS complementary feeding method in this specific population, generating data to support families and healthcare providers.

**Trial registration:**

Brazilian Clinical Trials Registry (ReBEC): RBR- 229scm number U1111-1226-9516. Registered on September 24, 2019.

## Background

Complementary feeding (CF) is the process of introducing solid and liquid foods other than breast milk or infant formula to an infant’s diet [1]. The CF period represents the transition from milk feeding to solid foods [2]. Over the past half-decade, researchers have started to conduct studies about specific approaches to CF [3–10]. In the last decade, an alternative approach named Baby-Led Weaning (BLW) which consists of allowing the infant to make their own food choices, deciding the quantity and sensory characteristics of food according to their own energy needs, has been widely disseminated through digital media [11]. This method suggests offering food in pieces, strips, or sticks and claims that CF should not be influenced by the imposition of caregivers, who generally assume what and how much food the child needs and wants [12]. Currently, the Brazilian guideline recommends traditional spoon-feeding based on responsive feeding and suggests that soft foods can be offered to the child to handle if they are large pieces, and that meals have their consistency gradually progressed until, at twelve months of age, they reach a food consistency used by the child family [13].

Considering several questions raised by parents and healthcare professionals regarding the BLW method, such as possible risks of choking and inadequate supply of iron and calories, a group of New Zealand professionals created a modified version of this approach, which they named Baby-Led Introduction to SolidS (BLISS). The BLISS recommendations are the same as those of the BLW method, with some additional advice, including offer food shaped in large pieces, which the infant can hold by himself; guarantee one source of iron-rich food at each meal; offer a high-calorie food at each meal; offer prepared foods in a texture that reduces the risk of choking, and avoid foods listed as high risk of aspiration; always try the food before offering it to the infant, to check it does not become solid in the oral cavity; avoid round or coin-shaped foods; and ensure that the infant is seated, erect, and under supervision of an adult. A study compared the BLW and BLISS approaches, where BLISS participants received two intervention visits, resources, and on-call support, while BLW participants received no intervention. Findings showed that the BLISS intervention allowed to increase the offerings and variety of iron-containing foods and to reduce the offering of high-choking-risk foods [14].

Although the Brazilian guideline for CF has been reviewed and republished recently, the conventional method, Parent-Led Weaning (PLW), is still advised, and there are no recommendations for a baby-guided approach in Brazil [13]. Likewise, the current World Health Organization (WHO) guidance proposes pureed foods in the early stages of CF, with consistency progressing gradually along the first year of life [15]. Within this context, the present study intends to contribute to the following outcomes:

### Growth faltering

A nutritionally adequate diet is essential throughout childhood and especially crucial in the first 3 years of life, which are a critical period for growth faltering [13, 15]. Previously known as failure to thrive, growth faltering is defined as a current weight or rate of weight gain lower when compared to those of average children of the same age and sex [16]. It is related to many organic and nonorganic causes, including oral and motor function, which has raised concerns among healthcare professionals as to how efficiently an infant would be able to self-feed in terms of quantity as well as how motivated an infant would be to lead the feeding process [17].

It is still unclear whether a Baby-Led method would interfere with the growth process. The evidence available to date has not found any children with faltering growth, nor any significant differences in growth rate between the CF groups at 12 months, although recommendations about offering a high-calorie food with each meal were given [18]. Another study was designed to analyze this outcome [19], however, did not use the BLISS recommendations for energy intake, and assessed different ages. A case-controlled study examined children aged 20 to 78 months and found that spoon-fed ones appeared to be more obese (*z*-score > + 3), while the incidence of underweight (*z*-score < − 3) was higher in the BLW group [9]. A year after this study, a longitudinal investigation of self-reported weight in a sample aged 18 to 24 months found that children weaned with the standard method were more likely to be overweight (19.12% versus 8.1% in the BLW group) [20].

### Iron deficiency

Infants are vulnerable to anemia, especially iron-deficiency anemia (IDA), which represents a major public health problem with definite impacts on population health [21]. The literature suggests that early eating practices play an important role in the prevalence of iron deficiency [22]. Anemia is defined as the condition in which the blood hemoglobin concentration is two standard deviations below the reference for age, sex, and height [23]; 50% of cases are due to iron deficiency. It is estimated that about 25% of Brazilian children under age 3 years have IDA, and the promotion of breastfeeding, healthy eating habits, and prophylactic iron supplementation have long been employed as strategies to prevent this condition [24].

BLISS method does not appear to increase the risk of iron deficiency in comparison to PLW when parents are advised to offer high-iron foods in each meal [25]. Given the evidence of IDA in this age group and the scarcity of published studies on infant-guided feeding introduction methods (none in the Brazilian population), systematic investigation and evaluation of anemia in early childhood are particularly important.

### Feeding behavior

The feeding styles of caregivers and choice of CF method may influence the complex process of eating behavior [26, 27]. Caregivers’ encouragement of healthy eating and the responsibility and supervision of feeding was associated with reasonable children’s eating behaviors, especially low children’s emotional eating, infrequent satiety responsiveness, and food fussiness behaviors [27]. The authoritative style of parenting has a significant negative direct effect on children’s including emotional overeating and food fussiness [28]. Additionally, high parent-centered feeding along with high child-centered feeding styles was associated with improved diet quality and the lowest percentage of overweight and obese children in a study of Latino families [29].

A study of 565 parents with toddlers aged 12 to 36 months in the United Kingdom found that parents who were following a strict, predominantly BLW style used less instrumental feeding practices, exerted significantly less control over their toddler’s eating, used significantly less encouragement to increase food consumption, shared their mealtimes, and ate the same meals with their children [30]. The food preferences developed at this age have a long-lasting impact. Combined with the stress surrounding infant feeding decisions, feeding advice for parents must be aligned with appropriate expectations regarding effects on eating behavior.

### Dietary quality

A Baby-Led approach to complementary feeding has been suggested to increase dietary variety and exposure to more textured foods at a young age. According to Morison et al. (2018), at 7 months of age, BLISS participants had greater total food variety with no difference in fruit and vegetable variety. However, at 24 months of age, BLISS children had greater variety in fruits and vegetables compared to traditionally spoon-fed children [31].

BLW researchers suggest that a baby-guided approach leads to healthier food choices, since there is greater fruit and vegetable exposure and variety, as well as greater participation in family meals [4, 32]. However, few studies have investigated whether baby-guided approaches influence food variety [3, 8, 33].

### Feeding difficulties

The prevalence of feeding difficulties in childhood ranges from 20 to 35% [34] and represents a high-impact clinical problem for children and families alike [35]. The consequences of these difficulties include growth faltering, malnutrition, lethargy, developmental delay, aspiration, invasive medical procedures (such as feeding tube placement), and hospitalization [36].

Children with feeding difficulties, such as food neophobia or picky eating, consume fewer fruits and vegetables, have a lower-variety diet, and weigh in at lower percentiles [37]. In addition to their potential impact on physical well-being and development, eating problems are associated with parental stress, emotional well-being, and parent-child interactions [38]. To the best of our knowledge, the evidence published to date has not yet analyzed the influence of different CF approaches on the prevalence of feeding difficulties.

### Food preferences

The strongest predictors of food preferences in childhood are whether the child likes how food tastes; how long they were breastfed, and, while breastfeeding, what their mothers were eating; and whether they were offered and ate these foods at an early age [39]. Therefore, food choices are strongly associated with sensory properties, leading to acceptance or aversion to certain foods [40]. The sensation of flavor is formed by a complex combination of taste, smell, and somatosensory information [41].

Variations in taste perception among individuals can also shape flavor preferences, influencing dietary intake and long-term eating habits [42]. Studies have demonstrated that genetic variations related to bitter taste, for instance, may be related to acceptance of feeding introduction [43], to food selectivity [44], and higher daily energy density from snacks in children aged 3 to 5 years [45]. Regarding sweet taste, research has related the TAS1R2 and TAS1R3 receptors to changes in preference for sweet taste and eating behavior, higher risk of cavities, and greater consumption of carbohydrate-rich foods [45, 46]. However, no studies have explored the impact of different forms of feeding introduction and environmental modulation on acceptance of specific flavors in childhood while analyzing associated genetic polymorphisms as well.

### Oral habits

The prevalence of dental caries in individuals up to 3 years of age in different Brazilian cities has been reported to range from 11 to 29% [47, 48]. Sucrose is known to be an essential risk factor for the development of this disease [49]. The age of onset of sucrose exposure appears essential; dietary factors observed before age 12 months are associated with severe early childhood caries (S-ECC) at preschool age [50, 51]. Duration and type of breastfeeding also appear to influence the experience of dental caries [51, 52].

Otherwise, results of a study in which researchers used electromyography suggest that the muscle activity of infants who are breastfed exclusively renders them less likely to develop dysfunctional muscular patterns that might predispose bottle-fed infants to develop a malocclusion [53].

A study that compared baby-led weaning with the traditional method demonstrated that the former was associated with lower odds of exposure to sucrose and processed foods [54], which could contribute to better oral outcomes. Therefore, our intention in evaluating oral habits is to investigate whether feeding methods could lead to different oral outcomes in our population. We are not aware of any published literature on the effects of baby-guided CF on dental caries or gingival inflammatory status.

### Choking

Parents, caregivers, and health professionals often express concern regarding the risk of choking associated with CF methods, especially the BLW. First, it is prudent to differentiate choking/asphyxiation from the gag reflex, which is a normal physiological condition. In a review that addressed the theme, there was no difference in the proportions of choking/asphyxiation between those who adhered to the BLW strategy and those exposed to traditional eating behavior, despite the fear in the discourse of parents and health professionals [55]. Clinical studies also found no difference and reported a small number of severe choking/asphyxiation events in both groups [56, 57]. Regardless of the CF method, it is important to emphasize that parents/caregivers should offer safe food in appropriate environments, as well as to know how to correctly manage babies in case of choking [56].

### Functional constipation

Functional constipation (FC) is a frequent complaint in pediatric clinics, with a worldwide prevalence in children ranging from 0.5 to 32.3% [58]. In addition to impacting the quality of life of these children and their families, the process of diagnosis and treatment of FC is financially demanding on health systems [59]. Factors that can contribute to FC include pain, fever, dehydration, food and fluid intake, psychological issues, toilet training, medications, and family history of constipation [60]. The lack of data in the literature on the impact of different CF methods on the amount of fiber ingested and the consequences of this intake for intestinal health makes the study of this outcome important to guide future recommendations.

## Methods/design

### Study design

The study will consist of a three-arm controlled trial (Fig. 1), which will intend to randomize mothers and their respective infants into three different groups of CF: (A) strict Parent-Led Weaning (PLW), which is the control arm; (B) strict Baby-Led Introduction to SolidS (BLISS); and (C) mixed method: a combination of PLW and BLISS created especially for this study. Three interventions will be performed throughout the study, and measurement of the main outcomes is expected at 12 months of age. The framework expected to the outcomes is that BLISS and mixed methods will be superior to the PLW method.

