**Fig. 1 Fig1:**
[figure not shown]
Study design flow chart. PLW, Parent-Led Weaning; BLISS, Baby-Led Introduction to SolidS. Adapted from Daniels et al. (2015) [18]

This study has been approved by Hospital de Clínicas de Porto Alegre (HCPA) Ethics Committee (under number 2019-0230, CAAE: 1537018500005327) and is currently registered in the Brazilian Clinical Trials Registry (ReBEC) with accession number RBR- 229SCM. The protocol was written according to SPIRIT guideline, and its checklist was carried out (Additional File).

Written informed consent will be obtained from all responsible of the participants before randomization. This document specifies all steps carried out in the research, as well as the consent to publish the data and the confidentiality, making it clear that the results will be presented together, without identifying or naming the participants. The research team will clarify all participants’ questions about the research procedures before signing the consent form. The research will bring direct benefits of nutritional support to participant children, as well as clarify any doubts expressed by mothers at the start of the study and throughout the study period, until age 12 months. A survey will provide feedback on nutrition assessment results and laboratory tests, by e-mail or letter; in case of relevant changes, a copy will be forwarded to the referral health unit. If any nutritional deficit or excess is detected, the child will be referred to an appropriate health care provider.

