### Outcome measures

*Z*-scores of anthropometric measurements (weight for age, weight for length, length for age, and BMI for age *z*-scores) will be our primary outcome measure to investigate child growth and nutritional status. As secondary outcomes, we will analyze choking prevalence, dietary variety, food and flavor preference, child and parent feeding behavior, iron deficiency, oral hygiene behavior, dental caries, dental development, gingival health status, the prevalence of functional constipation, maternal perception of the CF methods, and prevalence of child eating disorders.

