### Statistical analysis

The database will be prepared in SPSS (Statistical Package for the Social Sciences) version 21.0, with double entry and validation. Descriptive analyses of continuous and categorical variables will be performed, in the isolated 10% quality assurance sample and in the total sample. Parametric data will be expressed as mean ± standard deviation. All analyses will be conducted by the intention-to-treat principle. The primary analysis will determine whether PLW, BLISS, or the mixed method results in differences in child growth *z*-scores at 12 months of age. Regression analyses will be used to analyze secondary outcomes, including iron intake and status. We will consider adjusting plasma ferritin where there is evidence of infection or inflammation, as indicated by elevated CRP. Statistical significance will be accepted at *p* < 0.05.

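### The article declares superiority across the outcomes, but the primary growth z-scores have no stated favourable direction and are analysed only for differences

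*Protocol article*

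**What the plan says.** - **Framework (Study design).** "The framework expected to the outcomes is that BLISS and mixed methods will be superior to the PLW method". The sentence follows the one that places the main outcomes at 12 months. It exempts no outcome and gives neither a direction nor a margin.
- **Primary outcome (Outcome measures).** Z-scores for weight-for-age, weight-for-length, length-for-age and BMI-for-age "will be our primary outcome measure to investigate child growth and nutritional status".
- **Primary analysis (Statistical analysis).** "The primary analysis will determine whether PLW, BLISS, or the mixed method results in differences in child growth" z-scores at 12 months, with significance at p < 0.05. No direction is given.
- **Aim (Abstract, Discussion).** To "ascertain whether there are potential advantages to the BLISS complementary feeding method".
- **Both ends of the scale are unfavourable.** In the Growth faltering section, one earlier study is cited in which "spoon-fed ones appeared to be more obese" while underweight was more frequent with baby-led weaning. The Study design section adds: "If any nutritional deficit or excess is detected, the child will be referred to an appropriate health care provider". The Adverse events section monitors growth faltering at 9 and 12 months.
- **Prior evidence (Growth faltering).** Earlier work is reported to have found no faltering "nor any significant differences in growth rate between the CF groups at 12 months".

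**The concern.** Superiority needs a direction in which one result is better than another. For a mean weight or BMI z-score in healthy term infants, a higher value may mean less faltering or more overweight, and a lower value the reverse. The article raises both worries and does not say which shift would count in favour of BLISS. A lower BMI z-score under BLISS could be presented as protection against overweight or as impaired growth, and the text does not settle which.

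The Growth faltering section also poses what is in effect a safety question: whether a baby-led method interferes with growth. Given the earlier evidence it cites, a non-significant result is quite possible. A superiority framework gives such a result no meaning beyond superiority not having been shown, and the only decision rule printed is p < 0.05. What is at stake is what the trial may conclude from its primary outcome, whichever way the result falls.

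**Working it through.** **1. The passages side by side**

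| Element | Place | Direction |
|---|---|---|
| Framework | Study design | BLISS and mixed better than PLW |
| Primary outcome | Outcome measures | none stated |
| Primary analysis | Statistical analysis | none (differences) |
| Effect for sizing | Sample size | none (unsigned) |
| Low growth | Growth faltering, Adverse events | unfavourable |
| High growth | Growth faltering, Study design (referral for excess) | unfavourable |

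The link from superiority to the z-scores runs through the Outcome measures section, since the framework sentence speaks of the outcomes in general.

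**2. The plan's own figure**

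Inputs from the Sample size section: half an SD, SD 1, 80% power, 5% significance, 48 per arm. With n per arm = 2 × [(z_α + z_β) × SD / δ]², normal approximation:

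- One-sided: 2 × [(1.645 + 0.842) / 0.5]² = 49.5, so 50 per arm. Power at 48 is Φ(0.5/0.204 − 1.645) = 78.9%.
- Two-sided: 2 × [(1.960 + 0.842) / 0.5]² = 62.8, so 63 per arm. Power at 48 is Φ(0.5/0.204 − 1.960) = 68.8%.

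On the half-SD reading, 48 is approximately recovered only with a one-sided test, which would itself need a favourable direction. The section does not state sidedness. It also gives the effect as 0.8 kg/m² with SD 1, which is not half an SD; that is a separate matter. The present point does not depend on how 48 was obtained.

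**3. What a non-significant result would leave open**

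For a pairwise difference with 48 per arm and SD 1:

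- SE = √(2/48) = 0.204.
- 95% half-width = 1.96 × 0.204 = 0.40 z.
- An observed difference of exactly zero gives −0.40 to +0.40 z.
- An observed difference of 0.35 z is non-significant (0.35 < 0.40) and gives −0.05 to +0.75 z, which extends beyond the half SD used for sizing.

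This is without baseline adjustment, which the article does not mention. If baseline were adjusted for, with an assumed correlation of 0.7, the half-width would be 0.40 × √(1 − 0.49) = 0.29 z. Losses to follow-up would widen either figure.

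**The case against.** The strongest reply is that this is a mismatch of wording. The framework sentence does not name z-scores. Many secondary outcomes do have an obvious good direction: choking, iron deficiency, caries, constipation, dietary variety. The text that governs the primary analysis is already non-directional, and a significant result would support exactly what it asks. Interval reporting and the reading of a null result are commonly left to a statistical analysis plan, which is not shown.

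Much of this stands, and it rules out several stronger readings:

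- A reader might infer that no primary result could support any conclusion. A significant result would support the statement that the methods differ; it is superiority that it cannot support.
- A reader might infer that the investigators intend to read p > 0.05 as proof that BLISS is safe for growth. The article nowhere says so.
- A reader might infer that the plan regards half an SD as the smallest important difference. The Sample size section gives it only as the difference to detect.

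The reply does not remove the conflict. The framework is declared for the outcomes without exemption, and the primary outcome is among them. A later analysis plan could add detail, but the article itself has fixed a framework that does not fit its primary outcome.

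**Conclusion.** The point holds as an inconsistency in what the article states. The superiority framework does not fit growth z-scores that have no stated favourable direction and for which deficit and excess are both treated as harmful, and it conflicts with the non-directional primary analysis. A significant shift in mean z-score shows a difference only. A non-significant one, with an unadjusted 95% half-width of about 0.40 z, leaves differences of several tenths of a z-score open and does not by itself show unaffected growth.

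The size rests on SD 1 and 48 analysed per arm, both from the Sample size section, and on no baseline adjustment. The inconsistency rests on no numerical assumption. A favourable direction could be defined, for example closeness to zero or fewer children outside a stated range, but the article defines none. The point should be corrected; it does not invalidate the design.

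**What to change.** 1. In Study design, limit the superiority statement to named secondary outcomes with a clear good direction. For growth, state a two-sided hypothesis that the methods differ, in line with the Statistical analysis section.
2. Report the BLISS–PLW and mixed–PLW differences in each growth z-score with 95% confidence intervals.
3. Report the proportions of children in both the low and high z-score tails, with cut-offs named in advance. The article mentions z-scores beyond ±3 only when describing an earlier study and sets none of its own.
4. State that p > 0.05 alone will not be read as no effect on growth.

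If the investigators want to claim equivalence, the margin needs its own justification. ±0.5 z should not be adopted merely because it was the detectable difference: it would tolerate a deficit approaching half a z-score. It would also often fail at this size. With a true difference of zero, the chance that an unadjusted 95% interval lies within ±0.5 z is 2Φ((0.5 − 0.40)/0.204) − 1, about 38%.

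The cost is wording and reporting; the data and the 144 pairs are unchanged. The downside is that neither superiority nor safety could be claimed from the growth p-value alone. Stating the test as two-sided also makes explicit that 48 per arm gives about 69% power for half an SD, not 80%.
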